## Abstract

**Background:**

Currently, health care and medical decision-making at the end of life for older people are often insufficiently patient-centred. In this trial we study the effects of Advance Care Planning (ACP), a formalised process of timely communication about care preferences at the end of life, for frail older people.

**Methods/Design:**

We will conduct a cluster randomised controlled trial among older people residing in care homes or receiving home care in the Netherlands. The intervention group will receive the ACP program Respecting Choices® in addition to usual care. The control group will receive usual care only. Participants in both groups will fill out questionnaires at baseline and after 12 months. We hypothesize that ACP will lead to better patient activation in medical decision making and quality of life, while reducing the number of medical interventions and thus health care costs. Multivariate analysis will be used to compare differences between the intervention group and the control group at baseline and to compare differences in changes after 12 months following the inclusion.

**Discussion:**

Our study can contribute to more understanding of the effects of ACP on patient activation and quality of life in frail older people. Further, we will gain insight in the costs and cost-effectiveness of ACP. This study will facilitate ACP policy for older people in the Netherlands.

**Trial registration:**

Nederlands Trial Register: NTR4454.

## Background

The number of Europeans over 65 years of age will double in the next 50 years. To enable countries to successfully manage the dynamics and health care costs of their ageing populations, the WHO has proposed an “active ageing approach”, based on the United Nations Principles of independence, participation, dignity, care and self-fulfillment [1]. It targets government decision-makers at all levels, the nongovernmental sector and the private sector, all of whom are responsible for the formulation of policies and programs on ageing. It focuses on the activation of older people and is aimed at timely recognition and consideration of people’s health care preferences and needs to enable strategic planning and decision-making by older people themselves. Communication about people’s needs and preferences is typically postponed until acute events necessitate short-term medical decision-making. Sharp et al. showed that the majority of frail, older people would like to get the opportunity to timely discuss end-of life care. However, most of them do not have this opportunity [2].

Advance Care Planning (ACP) is a formalised process of communication between patients, their relatives and professional caregivers about patients’ health preferences, goals and choices [3]. Its central aim is to activate people to participate in decision-making about their health care and to raise awareness of the need to anticipate future deterioration of health. Patients are encouraged to appoint a surrogate decision-maker, and to document their wishes about their preferred care in an advance directive. In this way, written advance directives extend the autonomy of patients to a phase when they are incompetent [4].

Several studies have assessed the outcomes of ACP programs. In der Schmitten et al. studied the effects of implementing a regional ACP program in German nursing homes and concluded that the implementation led in many cases to the completion of advance directives with potential relevance to medical decision-making [5]. Some reviews showed that ACP is associated with better patient outcomes. In a recent systematic review, Brinkman-Stoppelenburg et al. showed that some ACP programs are associated with a reduction in futile measures and unnecessary hospitalizations [6]. The programs contributed to better communication between patients and health care professionals and higher quality of life of both patients and their relatives. Furthermore, extensive ACP interventions seemed to increase compliance with patient wishes and satisfaction with care more than just the completion of advance directives. According to the review of Brinkman-Stoppelenburg et al. extended programs such as e.g. the Respecting Choices program are the most promising ACP programs [6]. In another systematic review, Houben et al. showed that ACP programs facilitated completion of advance directives and end-of-life discussions between patients and health care professionals. The programs improved concordance between preferred and delivered care and potentially improve other outcomes as well, such as quality of communication [7].

Overall, we can conclude that ACP programs have beneficial effects on several patient outcomes. However, evidence on the effects of ACP programs in care homes and in community dwelling older people is scarce [6, 7]. Furthermore, few studies concerned a randomized controlled trial, although this is the most preferred method of studying effects of interventions in health care. Finally, most of the studies were performed in the US. Previous research showed that end-of-life decision-making varies largely between countries [8]. It is unknown to what extent results from the US can be generalized to European countries like the Netherlands, given the differences in health care systems.

Also, research on the costs of ACP is limited, although the cost-effectiveness of health care interventions at the end of life is an important issue due to the fact that end-of-life care is often expensive. While health care costs in an average life year have been found to amount to 1100 € per person, costs per last year of life were 13,5 times higher and approximated 14,900 € per person according to Polder et al. [9]. Molloy et al. assessed the costs of an ACP program in a randomized controlled trial in Ontario, Canada. Intervention nursing homes reported fewer hospitalizations per resident, a lower hospital length of stay ensuing reduced hospital care costs and lower total health care costs than control nursing homes [10]. We are not aware of any formal cost-effectiveness studies on ACP programs in care homes or nursing homes in Europe.

We will perform the first cluster randomized controlled trial on the effects of ACP in frail, older people in the Netherlands. The main objective of this project is to assess the effects, the costs and the cost-effectiveness of ACP. Participants in the intervention group will be offered the Respecting Choices program, one of the most promising ACP programs (see below for further information about the program) [6, 11]. We focus on older people living in care homes or living at home and receiving home care. We hypothesize that ACP will lead to better patient activation in medical decision making and quality of life in the intervention group compared to the control group, while reducing futile interventions and thus health care costs.

## Methods/Design

### Study design

We will conduct a cluster Randomized Controlled Trial (RCT) among older people living in care homes or at home receiving home care, following the CONSORT guidelines. The clusters will consist of neighbourhoods. In the Netherlands, standardized household incomes have been calculated per neighbourhood. We will order neighbourhoods according to these standardized incomes to control for differences in income per study arm, since income is related to health [12]. Neighbourhoods will be randomized per set of two neighbourhoods with comparable household incomes to either the control or intervention condition.

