### Sample size

We aim at an overall power of 0.8 (alpha 0.05) to detect a difference of at least 0,5 SD in the Patient Activation Measure. We consider 0,5 SD to be a clinical relevant difference based on the article of Norman et al. [25]. To be able to detect such a difference we need 63 individuals in each arm in a non-clustered study. We used a multiplication factor of (1 + (k-1)*ICC), with k indicating the average cluster size, which is 12, and ICC indicating the intraclass correlation, which is the fraction of total variation in the data that is accounted for by between-group variation. For an ICC of 0.05 this amounts to a multiplication factor of 1.55, and thus 98 (1.55*63) individuals in both the intervention and the control arm.

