### Statistical analysis

Analyses will be performed following the intention-to-treat principle. Descriptive statistics will be used to summarize characteristics of the residents, the care homes and of people receiving home care. Characteristics of participating individuals (age, gender, socio-economic status, educational level) will be compared at baseline between the intervention and control (usual care) group using independent sample t tests and Chi^2^ tests.

Multivariate analysis will be used to compare differences between the intervention group and the control group at baseline and to compare differences in changes after 12 months following the inclusion. Patient characteristics, TFI score, MMSE score and place of residence will be used as covariables. All statistical tests will be considered significant if *p* < 0.05. Missing items will be imputed by the peoples’ own average score if they have completed at least 50 % of the items.

The cost-effectiveness of ACP will be assessed by calculating the incremental cost-effectiveness ratio (ICER), defined as the difference in costs of ACP compared to usual care, divided by the average change in effectiveness, with the patient activation as primary outcome measure [17]. We will perform a sensitivity analysis to assess the stability of the results to changes in costs and effectiveness parameters. Because of the short time horizon, costs and effects will not be discounted.

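### Neighbourhoods are randomised in income-matched pairs, but the listed covariables include neither the pair nor neighbourhood income, so possible precision is forgone and standard errors are conservative

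*Protocol article*

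**What the plan says.** The Study design section of the protocol article makes the neighbourhood the unit of randomisation: "The clusters will consist of neighbourhoods". It restricts the allocation on a neighbourhood-level variable and gives the reason: "We will order neighbourhoods according to these standardized incomes to control for differences in income per study arm, since income is related to health". The restriction is by pairs: "Neighbourhoods will be randomized per set of two neighbourhoods with comparable household incomes to either the control or intervention condition".

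The Statistical analysis section names the type of analysis only in general terms: "Multivariate analysis will be used to compare differences between the intervention group and the control group at baseline and to compare differences in changes". It then gives an adjustment set: "Patient characteristics, TFI score, MMSE score and place of residence will be used as covariables". What counts as a patient characteristic is not spelled out in that sentence. The same section does list individual characteristics for the baseline comparison: "Characteristics of participating individuals (age, gender, socio-economic status, educational level) will be compared at baseline". Place of residence is not defined. Given the two recruitment settings, care home versus own home is the likelier meaning.

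The Sample size section inflates for clustering with the full unmatched design effect and takes no credit for matching.

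**The concern.** The investigators treat neighbourhood income as prognostic; that is their stated reason for pairing on it. The article then writes down an adjustment set that omits the one variable used to restrict the allocation. This goes beyond leaving detail to an analysis plan, because a list is given and the matching variable is not on it.

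Pairing makes the two arms more alike than simple randomisation of neighbourhoods would, so the estimated difference varies less from one possible allocation to another. A cluster model without the pair or the income variable cannot see this. It leaves the income-related variance between neighbourhoods in the residual, and its standard error describes an unmatched trial. At stake are intervals wider than they need be and some loss of power, in a trial with few clusters and little power to spare.

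**Working it through.** **Inputs from the Sample size section:** detectable difference 0.5 SD, power 0.8, alpha 0.05, 63 per arm unclustered, average cluster size k = 12, ICC = 0.05, 98 per arm.

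**Assumed:** r, the share of between-neighbourhood variance explained by neighbourhood income. The article gives no value, so a range is shown.

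**1. The plan's own figures.** n = 2(1.960 + 0.842)²/0.5² = 62.8, so 63 per arm (two-sided). Design effect = 1 + (12 − 1) × 0.05 = 1.55. Then 1.55 × 63 = 97.65, so 98 per arm. Both figures reproduce. Neighbourhoods per arm: 98/12 = 8.2, hence about 8 pairs.

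**2. Variance of the effect with matching.** In units where an unclustered trial has variance 1, the variance is k × ICC × (1 − r) + (1 − ICC).

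| r | Variance units | √(1.55/variance) |
|---|---|---|
| 0 | 0.60 + 0.95 = 1.55 | 1.00 |
| 0.25 | 0.45 + 0.95 = 1.40 | 1.05 |
| 0.5 | 0.30 + 0.95 = 1.25 | 1.11 |

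The last column is the ratio of the standard error that ignores income to the true spread of the estimate, if the two members of a pair share the income effect exactly. The between-neighbourhood part is 0.60/1.55 = 39% of the total, so it matters but is not the larger part.

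**3. Simulation with pairs formed by ordering on income.** Settings: 8 pairs, 12 people per neighbourhood, ICC 0.05, total SD 1, a linear income effect, equal cluster sizes, no dropout and no other covariables. At r = 0.5, the cluster analysis without income has a mean standard error of 0.178 against a true SD of 0.163. The ratio is 0.178/0.163 = 1.09, about 9% too wide. This is a little below the 11% from the formula, partly because neighbours in an ordered list are similar in income but not identical. At r = 0 there is no excess.

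**4. Power at 0.5 SD, and type I error, with clusters modelled.**

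| r | Power, no income term | Power, income as 1-df covariate | Change (points) | Type I error, no income term |
|---|---|---|---|---|
| 0 | 0.740 | 0.736 | −0.4 | about 0.05 |
| 0.25 | 0.741 | 0.771 | +3.0 | about 0.04 |
| 0.5 | 0.743 | 0.813 | +7.0 | 0.032 |

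With the covariate, type I error stays at 0.048 to 0.050. These powers come from cluster-level t-tests with few degrees of freedom, so they are not directly comparable with the 0.80 from the normal formula. The comparison that matters is across each row.

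**5. Pair-level analysis (7 df) against unmatched cluster analysis (14 df), power at 0.5 SD,** with the pair effect shared exactly: r = 0, 0.67 vs 0.74; r = 0.25, 0.71 vs 0.75; r = 0.5, 0.76 vs 0.75; r = 0.75, 0.81 vs 0.76. The pair-level analysis breaks even at about r = 0.5.

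**The case against.** The case on the other side is substantial, and most of it limits the point.

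- **The balance is not lost.** A reader might infer that the benefit of matching disappears. It does not. The stated aim is "We will order neighbourhoods according to these standardized incomes to control for differences in income per study arm", and the allocation delivers that whatever the model. Only a possible precision gain is forgone. The 98 per arm does not rely on such a gain.
- **The error is in the safe direction.** A reader might infer that the intervals are invalid or that false positives increase. In a cluster model without income, type I error falls below 0.05. Inflation would arise if neighbourhood clustering itself were ignored, which is a separate matter.
- **The size depends on an unknown.** The article says only that income is related to health. The outcome is patient activation, analysed as change over 12 months, so a stable income effect on the level could largely cancel. The useful value of r could be near zero.
- **Other covariables may do some of the work.** Socio-economic status may be in the model, and what matters for precision is variance explained, not whether the variable is the one used for pairing. This stands in part: it is an individual measure, whereas the matching variable is a neighbourhood figure, and the article does not say that it will be adjusted for.
- **Breaking the pairs can be sensible with so few.** This is right for a pair-level analysis, as step 5 shows. It does not apply to a single income covariate, which costs one degree of freedom instead of seven.
- **The article is condensed and the analysis plan is not shown.** A pair or neighbourhood term may be specified there. The remaining point is that the adjustment set in the article is explicit and leaves out the matching variable.

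**Conclusion.** The point holds in a limited form. The listed adjustment set does not follow the income-matched randomisation. In a model with a neighbourhood term, this makes the standard error about 0 to 9% too wide for r between 0 and 0.5. Adding income would change power by between −0.4 and +7 points over the same range. These figures rest on about 8 pairs of 12, an ICC of 0.05, a linear income effect, equal clusters, no dropout and no contribution from the other covariables. Any contribution from socio-economic status would shrink them. The documents do not support a claim that the trial would be biased, that its sample size is wrong, or that between-neighbourhood variation is the main source of uncertainty. This is an inexpensive improvement worth making, not a threat to validity.

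**What to change.** In the Statistical analysis section, or in the analysis plan if it is still open, add neighbourhood standardised household income as one continuous covariable, and state that the model accounts for neighbourhood clustering. Define place of residence, and say whether individual socio-economic status is among the adjusted patient characteristics. Name a pair-stratified analysis as a sensitivity analysis only. If the investigators prefer to leave income out, a sentence justifying analysis without the matching would be enough.

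The cost is a change of wording. The income figures are already held, because they are used to order the neighbourhoods. Statistically, the price is one of about 14 cluster-level degrees of freedom (2 × 8 − 2), which is under 1 point of power if income turns out not to be prognostic.

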### Study population

The study population consists of older people living at home and receiving home care or residing in one of 16 participating care homes of Laurens, a care organisation in Rotterdam, the Netherlands. Residents of care homes generally suffer from one or more chronic conditions and 32 % are totally dependent on others for daily care needs [13]. Their average life expectancy is 3,7 years, and their health condition often involves important health care decisions in a relatively short time frame.

### Inclusion criteria

In order to be eligible to participate in this study, an older person must meet all of the following criteria:≥75 years of age;Mentally competent, as measured by judgement of caregiver and a Mini–Mental State Examination (MMSE score > 16 [14];Fluent in Dutch;Being frail, as measured by the Tilburg Frailty Index [15] (TFI score of 5 or more)

These criteria apply for both people living in care homes and people living at home and receiving home care. Older people who move during the follow-up of the study can remain included in the study.

### Intervention

Older people in the intervention group will be offered the Respecting Choices program in addition to their usual care. This program, developed in the US, involves trained nurse facilitators who, in collaboration with physicians, assist residents and their relatives in reflecting on the resident’s goals, values and beliefs and in discussing their health care wishes [11, 16]. This discussion also supports people to identify specific activities and experiences that may contribute to, or detract from, their quality of life. Residents are encouraged to appoint a surrogate decision-maker, and to document their wishes about the care they do or do not want to receive in an advance directive. These wishes can e.g. concern the (non)use of burdensome life-prolonging interventions such as hospitalization or cardio-pulmonary resuscitation. For our study, a nurse practitioner followed the Respecting Choices train-the-facilitators program in the US. She will deliver the training program for the facilitators. These are nursing staff members of Laurens, who will deliver the intervention to the study participants. The intervention concerns two meetings of a facilitator with a participant of 1 h. The content of the communication during these meetings will be structured by the use of interview cards.

### Primary and secondary outcomes

The primary outcome measure is patient activation, which measures patient participation in medical decision making [17]. Secondary outcome measures are quality of life, satisfaction with health care, cost-effectiveness, use of burdensome medical interventions, appointment of a surrogate decision- maker and documentation of care wishes in advance directives.

### Assessment and data collection

At baseline, in personal structured interviews, patient activation will be measured (PAM-13) [17]. The PAM assesses patients’ knowledge, skill and confidence in self- management. Also, generic Health-Related Quality of Life as measured by the SF-12 [18] and satisfaction with health care as measured by the PSQ-18-SF6 [19] will be assessed.

At 12 month follow-up participants will be interviewed again and their competence will be assessed with an adapted version of the Mini-Cog [20]. If participants are competent, the questions of the SF-12 [18], PAM [17], and PSQ-18-SF6 [19] will be asked. We will also ask whether participants completed an advance directive and assigned a proxy decision-maker. In the intervention group, open (qualitative) questions will be asked about how the patient experienced the ACP program.

If the Mini-Cog indicates that participants are no longer competent, a proxy, assigned by the patient at the start of the study, will be approached for a telephone interview. This interview will include the PSQ-18-SF6 [19] and a caregiver activation measure (CAM) [21]. Completion of an advance directive and assignment of a proxy decision-maker by the participant will be assessed. In the intervention group, open (qualitative) questions will be asked about how the relative and the patient experienced the ACP program.

If people pass away during the 12 month follow-up, a proxy, assigned by the patient at the start of the study, will be approached for a telephone interview. This interview will address characteristics of the dying process, quality of dying [16], PSQ-18-SF6 [19], feelings of anxiety and depression of the relative as measured by the HADS [22]. In the intervention group, open (qualitative) questions will be asked about how the relative and the patient experienced the ACP program.

In a medical file study, we will investigate whether people have an advance directive in their medical file (and study its content). Moreover, we will study the medical care people receive during 12 months after inclusion, such as hospitalizations (number, length of stay), use of homecare, palliative care, diagnostic procedures and specific treatments (e.g. medication, mechanical ventilation, resuscitation, chemotherapy, artificial fluids or food, surgery or antibiotics).

Furthermore, an extensive economic evaluation of ACP will be performed from a health care perspective. For the calculation of the health care costs we will distinguish intramural and extramural medical costs. The unit price of the ACP program will be determined with the micro-costing method, which is based on a detailed assessment of all resources used [23]. Therefore, ACP facilitators will register their time investments per individual participant. Costs for inpatient days in care homes will be estimated as real, basic costs per day using detailed administrative information. For the calculation of other medical costs, we will use charges as published in Dutch guidelines as a proxy of real costs [24].

